### Randomisation and blinding

When all inclusion criteria have been met and informed consent has been obtained, participants will be randomly allocated to one of the two groups. Randomisation is based on a blocked randomisation sequence generated by a research statistician independent to the study team and with the sequence unknown to both researchers and participants. Two independent code keepers at MRC HNR, who are not involved in the running of the study, are securely holding the randomisation code. To maintain scientific integrity, at no point will those either generating or holding the study codes, come into contact with participants or data analyses. The details of the allocation are concealed from the research team and the participants until all data collection and analysis are complete. Blinding of participants and research team to allocation status will be assured by identical capsule appearance and identical labelling between the placebo and the active supplementation. Blinding of the capsules, packaging and labelling have been undertaken by the funding company (National Safety Associates (NSA) LLC, USA).

#### Capsule supplementation

Participants are asked to take six 00 capsules daily: three capsules twice with meals and plenty of water. The intervention supplements were made by blending three separate formulas. Two of these formulas contain a dried powder blend of juice and pulp of a number of fruits like apple, grape and blueberry, whereas the last one consists of vegetable juice powder and pulp from different vegetables such as carrot and broccoli. The total amount of nutrients contained per six capsules can be found in Table 1. The placebo capsules contain microcrystalline cellulose, dicalcium phosphate, magnesium stearate and FD&C yellow #6.

**Table 1 Tab1:** Intervention supplement nutritional value (per six capsules)

Nutrient	Active
B-carotene	1.8 mg
Vitamin E	22 mg
Vitamin C	300 mg
Folate	200 μg

### Study procedures

#### Recruitment and pre-screening questionnaire

Figure 1 summarises the National Safety Associates nutritional supplementation trial of fruit and vegetable extracts and vascular function (NNTV) recruitment and participant follow-up plan. Table 2 provides an overview of the study procedures performed at each visit.

**Fig. 1 Fig1:**
[figure not shown]
CONSORT flow diagram

**Table 2 Tab2:** Schedule of samples and data collection

Task	Pre-screening (telephone)	Screening	Test visit 1 (week 0)	Intermediate visit (week 6)	Test visit 2 (week 12)
Pre-screening questionnaire	X				
Obtain informed consent		X			
Study eligibility/screening	X	X			
Medical history		X			
Height, weight and BMI	X	X	X		X
Waist circumference			X		X
Body composition (bioelectrical impedance)			X		X
Spot urine sample (10 ml) for hydration status assessment including osmometry and including dipstick			X		X
24-hour urine collection			X		X
Physical activity questionnaire (IPAQ)		X	X		X
Standardised ‘5-A-Day’ advice		X	X	X	X
Group randomisation			X		
FACET (‘5-A-Day’/Lifestyle) Questionnaire		X	X	X	X
Blood pressure (standard automated at screening; seated, supine and ambulatory in TV1 and TV2)		X	X		X
Pulse wave analysis			X		X
Carotid intima-media thickness			X		X
12-lead ECG			X		X
and GTN-induced dilatation			X		X
Laser doppler iontophoresis			X		X
Assess continuance criteria			X	X	X
Blood samples		X	X	X	X
Assess concomitant medication	X	X	X	X	X
Test product dispensed			X	X	
Compliance assessment				X	X
Tablet count				X	X
Assess adverse reactions				X	X
Empty containers collected				X	X
Collect unused test product					X

Participants are recruited following one of the following methods: they are either identified from the MRC HNR volunteer database and are sent a letter inviting them to participate in the study, or they respond to a study advert placed around the community and in local magazines. Once the volunteer expresses initial interest in participating in the study, he/she is contacted via telephone by the study coordinator or research assistant. Both the participant information sheet (PIS), along with a leaflet describing all the vascular measurements used in the study, are sent to the potential participant, allowing them at least 24 hours to read and understand the study aim and procedures and decide if they would like to take part in the study.

The pre-screening telephone call lasts approximately 15 minutes and follows the structure of a standardised pre-screening questionnaire. The questionnaire assesses the potential eligibility of the participant for the study through a series of questions around the inclusion/exclusion criteria (including medication and self-reported height and weight) for the study.

Potential participants who are found not to be eligible will be excluded at this stage. Eligible participants will be invited to attend the study site (MRC HNR) for a further screening visit.

#### Screening visit

Following completion of the pre-screening questionnaire and provided that the participant is eligible to take part in the study, he/she is asked to attend the screening visit, which takes place at HNR and lasts approximately 2 hours.

Informed consent is obtained from all participants during the screening visit, and any questions relating to the study are answered, ensuring that the participant has fully understood all the study procedures before continuing. Consent is obtained before any measurements are taken. Height is measured to the nearest 0.1 cm using a stadiometer, and weight to the nearest 0.1 kg using calibrated mass scales. BMI is calculated using these measurements. Two blood pressure readings are recorded while the patient is in a seated position. A third BP measurement is performed if the first two readings have a discrepancy of more than 10 mmHg.

A full eligibility assessment is carried out using the HNR volunteer health screening and demographics questionnaire. Medical history and any recent changes in medication since the pre-screening questionnaire are also assessed and evaluated at this stage. In addition, female participants are also asked about the timing of their menstrual cycle as this can affect the vascular measurements in the study. Fasting blood samples are collected by venepuncture to measure blood lipids, glucose, and liver function as a routine safety measure and as an indicator of normal metabolism. Table 3 summarises all the blood markers that are examined during the study. At the end of the visit, the volunteers are asked to complete two short questionnaires: the International Physical Activity Questionnaire (IPAQ) and the Five-a-day Community Evaluation Tool (FACET) and are provided with ‘5-A-Day’ dietary advice. If successfully screened, the participant is invited back to complete test visits 1 and 2. Ineligible participants are thanked for their time and are offered to join the HNR volunteer database. Breakfast is provided to all potential volunteers before the end of the visit.

**Table 3 Tab3:** Blood parameters analysed in the National Safety Associates nutritional supplementation trial of fruit and vegetable extracts and vascular function (NNTV) study

	Biological parameter	Screening visit	Test visit 1 (week 0)	Intermediate visit (week 6)	Test visit 2 (week 12)
Screening/Safety and Research	FBC	X	X	-	X
	HbA1c	X	X	-	X
	HDL	X	X	-	X
	LDL	X	X	-	X
	Total cholesterol	X	X	-	X
	Liver function (ALT)	X	X	-	X
	Creatinine	X	X	-	X
	Fasting glucose	X	X	-	X
	Potassium	X	X	-	X
Research	Oxidized LDL		X	-	X
	C-Peptide		X	-	X
	Fasting insulin		X	-	X
	*Apo* A1		X	-	X
	*Apo* A2		X	-	X
	*Apo* B		X	-	X
	*Apo* E		X	-	X
	Cholesterol esters		X	-	X
	Oxysterols		X	-	X
	Isoprostanes		X	-	X
	P-Selectin		X	-	X
	E-Selectin		X	-	X
	IgM phosphorylcholine		X	-	X
	Vitamin A		X	X	X
	Vitamin C		X	X	X
	Vitamin E		X	X	X
	Carotenoids		X	X	X
	TMAO^d^		X	-	X
	LPS^e^		X	-	X
	DNA, Metabolomics and other relevant stored sample analyses		X	-	X
	Urine		X^a, b^	-	X^a, b^

(1). All screening bloods will be analysed at the Clinical Biochemistry and Immunology Laboratory at Addenbrooke’s Hospital. (2). Participants may be excluded from the study if screening/safety blood results are deranged. Spot urine collection: ^a^24 hour urine collection: ^b^(3) Additional 15-ml blood samples will be collected at test visit 1 for future DNA analysis and at test visit 2 for open profile metabolomics. FBC, full blood count; HDL, high density lipoprotein; LDL, low density lipoprotein; ^d^TMAO, trimethylamine-N-oxide; ^e^LPS, lipopolysaccharide

#### Pre-test visits 1 and 2

Participants are asked to collect their urine for 24 hours prior to test visits 1 and 2. Participant randomisation takes place prior to test visit 1.

#### Test visit 1

Test visit 1 lasts approximately 5 hours. Any changes to medication or health status are re-assessed in order to evaluate whether participants are still suitable to participate in the study. Height and weight are also measured as previously described, and BMI is calculated from these measures. Three waist circumference readings are taken, measured to the closest 0.1 cm with an anthropometric measuring tape. Body fat percentage, as well as total body water, are calculated using a four-point bioelectrical impedance Tanita BC-418.

Three blood pressure readings are measured in seated and supine positions before starting the cardiovascular measurements. Blood pressure is also measured using the ambulatory blood pressure (ABP) device, which is programmed to record readings every 15 minutes. In addition, fasting blood samples are collected during the visit to measure the blood markers mentioned in Table 3, including fasting blood glucose, as well as HbA1c. The following cardiovascular measurements with the following sequence are performed in a fasting state: carotid intima media thickness (cIMT), pulse wave analysis (PWA) using sphygmocor applanation tonometry, laser Doppler iontophoresis (LDI), 12-lead ECG, flow-mediated dilatation (FMD) and glyceryl trinitrate-induced vasodilation. In addition, participants provide a single urine sample, and a member of the study team will carry out a hydration check using an osmometer and urine dip stick in order to measure hydration status. Fluid intake is also monitored during the test visits 1 and 2. At the end of the visit, participants complete the IPAQ and FACET questionnaires and are provided with ‘5-A-Day’ dietary advice. Before participants leave, they are issued with 6 weeks supply of capsules. Breakfast/lunch is provided to all participants at the end of the visit.

#### Intermediate visit (6 weeks)

The intermediate visit takes place 6 weeks after test visit 1 and lasts approximately 1 hour.

During this visit, a member of the study team assesses any changes to medications or health status to ensure that participants are still suitable for the study. Participants return the batch of capsules given during test visit 1 and are given the next 6 weeks supply of capsules. Remaining capsules are counted in order to ensure compliance with the protocol. In addition, fasting blood samples are collected to further monitor compliance with the intervention by testing vitamins A, C and E and carotenoid levels. At the end of the visit, participants complete the FACET questionnaire and are also provided with the ‘5-A-Day’ dietary advice. Breakfast is provided at the end of the visit.

#### Test Visit 2

This visit is identical to test visit 1 except that participants are not provided with more capsules. At the end of the visit, participants are thanked for their time and given forms for reimbursement.

### Analytic vascular measurements procedures

#### Carotid intima media thickness (cIMT)

cIMT is performed using a B-mode ultrasound imaging of the right and left carotid arteries with 7.5 MHz linear array transducer. In a dark, quiet room, participants are in a supine position with their head turned 45 ^o^ in the direction opposite to the carotid artery being measured. Eight longitudinal images of the distal common carotid arteries (CCA) are obtained, four from each side. On completion of the measurements, the images are analysed by two members of the research team. The outcome variable is the mean CCA-IMT defined as the average of four measurements of the far wall IMT of the right and left CCA.

#### Pulse wave analysis (PWA)

Aortic augmentation index (AIx) is derived from the right wrist (radial pulse) using the SphygmoCor Vx version 7.01 (AtCor Medical, Sydney, Australia). The SphygmoCor device provides a quality index (QI), which represents reproducibility of the waveform, and any recordings with a QI < 80 are excluded. Because the AIx changes with heart rate, the software adjusts this value for a heart rate of 75 beats per minute (AIx@HR75).

#### Laser Doppler imaging following iontophoresis

Vascular changes related to microcirculatory flow and endothelial function are identified using the laser doppler imaging (LDI) technique (Moor Instruments, UK) with iontophoresis of acetylcholine (Ach) and sodium nitroprusside (SNP). The room temperature is set at 22 to 23 °C, and the measurement is taken from the participant’s right arm while he/she is in a seated position. Each drug is administered at increasing currents of 0 μA, 40 μA, 60 μA and 100 μA for 5, 10, 30 and 60 seconds, respectively. Cumulative dose response curves are analysed automatically by the built-in software (MoorVMS-PC software).

#### Electrocardiogram (ECG)

A 12-lead ECG is recorded in each participant with a 12-channel ECG machine (GEM MED, GEM heart one+, Cambridge, UK) on a paper with a speed of 25 mm/sec and 10 mm/mv standardisation. ECG waveforms are also saved in the gem heart viewer software (GEM MED, Cambridge, UK) for further examination and analysis if needed. ECG is performed once during test visits 1 and 2.

#### Flow-mediated dilatation and induced vasodilation using glycerol trinitrate

FMD is assessed in the brachial artery by high-resolution ultrasound and computerised edge detection system (FMD studio, Quipu srl, Pisa, Italy). All FMD measurements are performed while the participants are in a supine position with their right arm extended and in a quiet, darkened room kept at a relatively constant temperature (22 to 23 °C) to minimise the possible negative effect of environmental and physiological influences. The blood pressure cuff is placed on the right forearm, 1 to 2 cm distal to the elbow crease, and an ultrasound probe holder is used to hold the probe stable on the antecubital fossa. The brachial artery is continuously imaged using a 7.5-MHz probe in B-mode (Accuson X300, Siemens UK; with a VF 8-3 probe) at a depth of 3 cm. The brachial artery diameter is measured on acquired frames using Quipu software (Quipu srl, Pisa, Italy). Baseline brachial artery images and blood-flow velocity prior to occlusion cuff inflation are recorded for 1 minute. The occlusion cuff is then inflated to 200 mmHg for 5 minutes and released, thereby inducing reactive hyperaemia and endothelium-dependent vasorelaxation, which is monitored for 4 minutes. Following a 10-minute recovery period, endothelium independent dilation is monitored over a 5-minute period after sublingual administration of 300 μg glycerol trinitrate (GTN) spray. Flow-mediated and GTN-induced dilatation of the brachial artery are expressed as maximum percent dilatation following cuff deflation and GTN administration, respectively.

### Side effects and safety assessments

All participants are provided with a booklet where they can record any potential side effects. In case they develop severe side effects, they are advised to stop the supplementation and will be excluded from the study. All serious and non-serious adverse events and/or reactions involving capsules supplementation are logged by a member of the study team in a password protected database. In addition, any abnormal results of clinical importance detected during the course of the study (screening, test visits 1 and 2) will be reported by the HNR clinical team to the participant’s general practitioner (GP).

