### Sample size

The sample size calculation was performed according to cIMT changes over 12 weeks of supplementation. cIMT normal values in the general adult population (including overweight individuals) less than 65 years of age, range from 0.60 to 0.80 mm with a SD of 0.10 mm. [7]. Assuming a two-tailed t-test using a 5 % significance level (two-sided), a sample size of 37 in each group (74 participants in total) was determined to have 85 % power to detect a mean cIMT difference of 0.07 mm after 12 weeks of supplementation between the intervention and control groups, assuming a common SD of 0.10 mm. Allowing for a dropout rate of approximately 15 %, we aim to recruit 80 participants in total; *n* = 40 in the placebo and *n* = 40 in the intervention group.

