### Data analysis

A consort flowchart of enrolled participants will be provided, and the demographic characteristics recorded at the time of randomisation will also be described. Descriptive analysis will be conducted for all baseline variables to compare participants in both study groups. Results will be reported as means and standard deviations for continuous variables and frequencies with percentages for categorical variables. Two group comparisons for changes in primary and secondary outcome measures following 12 weeks of intervention will be made, assuming similar levels of variance between the two treatment groups and using two-tailed t-tests for normally distributed data. Paired t-tests will be used to assess within-group changes in study outcomes. Multiple linear regression models will be used to assess whether changes from baseline to 12 weeks were significant between the study groups. Regression analysis will be conducted, with adjustment for potential baseline confounding variables. Additionally, a sensitivity analysis will be performed, exploring variation in the standard deviation between the differences of the mean change in cIMT measurements. Exploratory within-group changes will also be assessed for each outcome measure.

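### Severe side effects end study participation as well as capsule use, so some randomised participants would probably be missing from the week-12 comparison

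*Protocol article*

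**What the plan says.** The rule stands in the protocol article under Side effects and safety assessments: "In case they develop severe side effects, they are advised to stop the supplementation and will be excluded from the study". It is mandatory and makes one event of two: stopping the product and leaving the trial.

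Four other places fix its effect.

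- **Timing.** The section on the pre-test visits says "Participant randomisation takes place prior to test visit 1". Under Test visit 1, the first six weeks of capsules are handed out at the end of that visit.
- **Outcome.** The abstract defines the primary outcome as the cIMT change from test visit 1 to test visit 2. Table 2 schedules cIMT at those two visits only.
- **Analysis.** Data analysis says "Two group comparisons for changes in primary and secondary outcome measures following 12 weeks of intervention will be made". It adds paired t-tests and regression models for the same changes.
- **Bloods.** A footnote to Table 3 says "Participants may be excluded from the study if screening/safety blood results are deranged". It names no visit. The block of tests labelled "Screening/Safety and Research" is marked at screening, week 0 and week 12.

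The article says nowhere that participants who stop capsules are followed up or analysed in their allocated group.

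**The concern.** A randomised comparison is protected because the groups are compared as they were formed. Removing people for something that happens after the first dose weakens that protection if the product itself can cause the event. Severe side effects are such an event. If they are commoner on one type of capsule, and those who suffer them differ in cIMT change, the two sets left at week 12 are no longer comparable. The trial would then describe the effect in people who tolerated the capsules rather than in everyone allocated to them.

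The safety objective is touched as well. It covers changes in liver function, routine bloods and ECG, and the week-12 values of those with severe side effects would probably be missing.

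This is stated text and not a gap left to an analysis plan. An analysis plan could define an as-randomised analysis set, but it could not recover week-12 measurements that were never taken.

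**Working it through.** **Does the rule act only after randomisation?** Yes. Randomisation precedes test visit 1 and capsules are issued at its end, so nobody can have a capsule side effect before randomisation.

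**Does it reach the primary result?** Probably. The change score needs a week-12 cIMT. Whether exclusion means no further visits or removal from the analysis, the participant contributes nothing to the comparison.

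**The plan's own figure.** Inputs from Sample size: difference 0.07 mm, SD 0.10 mm, two-sided 5 %, power 85 %.

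n per group = 2 × (1.960 + 1.036)² × (0.10/0.07)² = 2 × 8.98 × 2.04 = 36.6, rounded up to 37.

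This agrees with the statement that "a sample size of 37 in each group (74 participants in total) was determined to have 85 % power". The exact t-test gives 37.6 per group, and power of 84.4 % at 37. The figure is sound for its inputs, and the point does not depend on it.

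**Illustration 1: the product works.** Assumptions, none of them in the article: k of 40 active participants are excluded, no placebo participant is, those kept have the planned 0.07 mm effect, and those excluded would have had none.

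As-randomised effect = 0.07 × (40 − k)/40

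| k excluded | as randomised (mm) | estimated (mm) | overstatement |
|---|---|---|---|
| 1 | 0.0683 | 0.070 | 40/39 = 1.03, or 3 % |
| 2 | 0.0665 | 0.070 | 40/38 = 1.05, or 5 % |
| 4 | 0.0630 | 0.070 | 40/36 = 1.11, or 11 % |
| 6 | 0.0595 | 0.070 | 40/34 = 1.18, or 18 % |

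**Illustration 2: the product does nothing.** Illustration 1 gives no bias here, so a different assumption is needed: those excluded differ from those kept by d SDs in cIMT change, and again only the active arm loses people. The article gives no SD of change, so its 0.10 mm is used.

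Shift = (k/40) × d × 0.10 mm; standard error = 0.10 × √(1/(40 − k) + 1/40); type I error from the normal approximation.

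| k excluded | shift, d = 0.25 to 1.0 (mm) | true type I error |
|---|---|---|
| 2 | 0.001 to 0.005 | 5.0 to 5.6 % |
| 4 | 0.0025 to 0.010 | 5.1 to 7.2 % |
| 6 | 0.004 to 0.015 | 5.3 to 9.9 % |

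Check of the last corner: shift 0.15 × 1.0 × 0.10 = 0.015 mm; standard error 0.10 × √(1/34 + 1/40) = 0.0233 mm; ratio 0.64; type I error 9.9 %.

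**Reserve.** The margin is 80 − 74 = 6 participants, or 7.5 % of 80. Exclusions under this rule use it up.

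**The case against.** The strongest reply is that the sentence covers only severe side effects, which may be very few in a supplement trial in otherwise healthy adults, and that participants and staff are blinded. Both points count. Rarity keeps the bias small, as the top rows of both tables show. Blinding makes deliberate exclusion by arm unlikely, but it does not prevent exclusion caused by the capsules' own effects. It is also fair to say that the article does not define exclusion, so a missing week-12 visit is the likely reading and not a certain one.

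Three stronger readings are tempting, and the documents do not support them.

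- **That exclusion depends on the outcomes themselves, through the week-12 bloods.** The Table 3 footnote is discretionary and can be read as aimed at screening, where the bloods are described as a safety measure. For clinically important abnormal results at screening and both test visits, the stated action is a report to the general practitioner. No safety bloods are taken at week 6. Those at test visit 1 precede the first capsule, and those at test visit 2 are taken at the same visit as cIMT. Exclusion on the last would mean deleting collected data, which the article nowhere says will happen.
- **That people judged unsuitable at week 6 are removed.** The text says only that a team member "assesses any changes to medications or health status to ensure that participants are still suitable for the study". It states no consequence, and a condensed article may leave the continuance criteria to the full protocol.
- **That the safety objective loses the severe reactions.** The same section says that serious and non-serious adverse events are logged. What may be lost is these participants' week-12 bloods and ECG.

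**Conclusion.** The point holds for the side-effect rule. It is explicit, mandatory and applies only after randomisation, and it would probably remove participants from the primary comparison for a reason that the capsules may influence.

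The size cannot be derived from the article, which gives no rate of severe side effects; the 15 % in Sample size is dropout from all causes. The illustrations rest wholly on assumed one-sided exclusion, and on either zero benefit or an assumed difference in those excluded. A reader might take the 11 % and 18 % as the expected overstatement, but they are only what would follow if 4 or 6 active participants and no placebo participants were excluded. With one or two excluded, the effect on the result is minor.

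The Table 3 footnote adds an ambiguity about which visits it covers, not a demonstrated selection on outcome. The case for changing the rule is that it is cheap to correct, while missed week-12 measurements cannot be recovered.

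**What to change.** Separate stopping capsules from leaving the study.

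- **Side effects and safety assessments.** Replace the words on exclusion with a statement that participants who stop capsules are, if willing and where it is safe, invited to the scheduled week-12 visit and analysed in the group to which they were randomised. The advice on stopping capsules is not touched.
- **Data analysis.** State that the primary analysis includes every randomised participant with a week-12 cIMT, whatever their capsule use. A per-protocol analysis can be shown separately.
- **Table 3 footnote.** Reconcile it with the side-effects section by naming the visits it covers. Add that data already collected after randomisation are not removed from the analysis because of blood results. Which results should lead to what action is a clinical matter, and nothing is proposed on it here.

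The cost is a few sentences, to be put through the approval process of a trial that was enrolling when the article was submitted. The week-12 visit is already scheduled. The statistical downside is some dilution of the on-treatment effect, because people who stopped capsules are counted in their group; the per-protocol analysis would show how much.

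### As worded, the adverse-event log appears limited to capsule-related events, and no adverse-reaction check is scheduled at test visit 1, where GTN and iontophoresis are given

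*Protocol article*

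**What the plan says.** Under Side effects and safety assessments, the protocol article states: "All serious and non-serious adverse events and/or reactions involving capsules supplementation are logged by a member of the study team". The same section gives each participant a booklet for noting possible side effects, without saying when it is handed out. It also sends clinically important abnormal results from screening and both test visits to the general practitioner.

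In Table 2 the row "Assess adverse reactions" is marked at the intermediate visit (week 6) and test visit 2 (week 12). The rows "and GTN-induced dilatation" and "Laser doppler iontophoresis" are marked at test visits 1 and 2. The procedure text confirms that these are administered agents. Acetylcholine and sodium nitroprusside are delivered by iontophoresis, and in the flow-mediated dilatation section "endothelium independent dilation is monitored over a 5-minute period after sublingual administration" of GTN.

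The section on pre-test visits places randomisation before test visit 1, and the Test visit 1 section has the first capsules issued before participants leave that visit. The section on test visit 2 says: "This visit is identical to test visit 1 except that participants are not provided with more capsules".

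**The concern.** In a double-blind trial the least assumption-laden comparison of harms uses all events by arm, because at the time of recording nobody knows who took the active product and relatedness is a guess. If a capsule link is a condition of entry to the log, that guess decides what data exist. An event of an unexpected kind is the one most easily set aside as unrelated.

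The schedule raises a second question. The vascular challenges at test visit 1 come after randomisation and before any capsule is taken. A reaction to them has no capsule link on which to be logged, and no adverse-reaction check is marked at that visit to prompt for it.

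**Working it through.** The plan gives no event rate or expected count, so there is no figure to reproduce. The check sets the stated rule against the stated schedule.

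**1. Schedule, from Table 2**

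| Item | Test visit 1 | Week 6 | Test visit 2 |
|---|---|---|---|
| Adverse-reaction check | no | yes | yes |
| GTN-induced dilatation | yes | no | yes |
| Laser Doppler iontophoresis | yes | no | yes |
| Capsules dispensed | yes | yes | no |
| Compliance assessment, tablet count, empty containers | no | yes | yes |
| Unused product collected | no | no | yes |

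The challenges take place at two visits, and an adverse-reaction check is scheduled at one of those two.

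**2. Number exposed at test visit 1.** The Sample size section aims for 40 participants per arm: 40 + 40 = 80. Up to 80 participants therefore undergo the challenges at a visit without a marked check.

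**3. The two readings of the logging sentence**

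- *Capsule qualifier applies to events and reactions.* Someone must decide that an event involves the capsules before it is entered. A reaction to GTN or iontophoresis at test visit 1 falls outside the rule.
- *Capsule qualifier applies to reactions only.* All adverse events are logged, and a challenge reaction at test visit 1 is covered if someone notices it. Table 2 still schedules no prompt at that visit.

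The first reading is the more natural. The preceding sentence is about side effects of the supplementation, and the Table 2 row speaks of reactions rather than events. The second remains possible.

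**4. Other routes at test visit 1**

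- Reports to the general practitioner concern abnormal results, not symptoms.
- In the stated measurement sequence the ECG precedes flow-mediated dilatation and GTN, so it cannot show a GTN reaction.
- The re-assessment of health status is described at the opening of the visit, to confirm continued suitability.
- The booklet is open to any side effect, but has no stated issue date, and transfer from it to the database is still governed by the logging sentence.

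**5. What filtering does to the comparison.** Let the arms have a and b events, and let a share p of each be judged capsule-related. The log then holds p × a and p × b, with ratio (p × a)/(p × b) = a/b. With one common p, counts and precision fall but the expected ratio does not change. The ratio can change only if p differs between kinds of event that are unevenly spread over the arms. The article gives no value for p.

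**6. Test visit 2.** Apart from dispensing, the text makes it the same as test visit 1. Table 2 adds the adverse-reaction check, compliance assessment, tablet count, container collection and product return. The two do not match.

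**The case against.** **An article condenses the full protocol.** Event definitions, causality categories and reporting of procedure-related reactions commonly sit in the full document, and their absence here is no finding. That stands. But the logging rule and the schedule are stated in the article, and the point rests on what they say.

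**The blank at test visit 1 has an ordinary explanation.** The row sits among product rows, and no capsule has yet been taken. This is a fair account of why it is blank, but it does not supply a check for the challenges. If the row covers product reactions only, challenge reactions have no dedicated check at either visit.

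**Stronger readings that the article does not support.**

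- A reader might infer that unrelated events and challenge reactions are lost. The sentence is ambiguous, and the booklet is not limited to capsule effects.
- A reader might infer that challenge reactions are booked to the capsules. Nothing says so, and the challenges precede capsule issue at test visit 1.
- A reader might count the challenges at both test visits as unmonitored. Test visit 2 has a scheduled check.
- A reader might take the test visit 2 wording to mean that nobody asks about weeks 6 to 12. Table 2 marks the check there, and a visit identical to test visit 1 would still include its health-status question.
- A reader might conclude that filtering erases a harm signal. With equal filtering in both arms, what is shown is a loss of precision only.

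**Safety objective.** The named safety indicators are liver function, routine bloods and ECG, not event counts. This limits the weight of the point but does not remove it, since the article does set up an adverse-event database.

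**Conclusion.** The point holds in a limited form. The logging sentence appears to make a capsule link the condition of entry, and at best is unclear on this. A causality judgement may therefore precede recording, and the comparison of harms between blinded arms may rest on attribution-filtered events. Separately, up to 80 participants receive GTN and iontophoresis after randomisation at a visit with no scheduled adverse-reaction check and no clear recording route beyond the booklet.

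This rests on the natural reading of the logging sentence, on recruitment reaching the target of 80, and on the full protocol not already stating a broader rule. How many events would be affected cannot be derived from the article. The cIMT comparison and the other efficacy analyses are untouched. The mismatch over test visit 2 is a minor matter of wording.

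**What to change.** 1. Reword the sentence under Side effects and safety assessments so that every serious and non-serious adverse event, from the start of test visit 1 to the end of test visit 2, is logged whatever its suspected cause.
2. Record relatedness as a separate field, completed while blinded, with the options capsule, study procedure and unrelated.
3. Add an adverse-event mark at test visit 1 in Table 2, placed so that it follows the vascular challenges.
4. Summarise all logged events by arm, with those judged capsule-related as a subset.
5. Reconcile the test visit 2 text with Table 2, naming the adverse-reaction check, compliance assessment, tablet count and product return.

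The cost is a reworded sentence, one table mark, one database field and a corrected line of visit text, plus a few more minor unrelated events to record. No visit is added. Enrolment was under way when the article was submitted, so the date of the change should be noted. If the full protocol already logs all events, only the article's wording and table need correcting.
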